## Abstract

**Introduction::**

Anastomotic leakage (AL) accounts for a significant proportion of morbidity following oesophagectomy. Endoluminal negative pressure (ENP) therapy via a specifically designed polyurethane foam (EsoSponge^®^, B.Braun Medical, Melsungen, Germany) has become the standard of care for AL in many specialized centres. The prophylactic (pENP) application of this technique aims to reduce postoperative morbidity and is a novel approach which has not yet been investigated in a prospective study. The aim of this study is therefore to assess the effect of pENP at the anastomotic site in high-risk patients undergoing minimally invasive transthoracic Ivor Lewis oesophagectomy.

**Methods and analysis::**

The study design is a prospective, multi-centre, two-arm, parallel-group, randomised controlled trial and will be conducted in two phases. Phase one is a randomised feasibility and safety pilot trial involving 40 consecutive patients. After definitive sample size calculation, additional patients will be included accordingly during phase two. The primary outcome of the study will be the postoperative length of hospitalization until reaching previously defined “fit for discharge criteria”. Secondary outcomes will include postoperative morbidity, mortality and postoperative AL-rates based on 90-day follow-up. A confirmatory analysis based on intention-to-treat will be performed.

**Ethics and dissemination::**

The ethics committee of the University of Zurich approved this study (2019-00562), which has been registered with *ClinicalTrials.gov* on 14.11.2019 (NCT04162860) and the Swiss National Clinical Trials Portal (SNCTP000003524). The results of the study will be published and presented at appropriate conferences.

## 1. Background

Anastomotic leakage (AL) is a life-threatening complication following visceral surgery. AL occurs in 5–30% of patients after esophagectomy and may be further complicated by mediastinitis, sepsis, multiple organ failure, or death [1,2,3]. Despite extensive research in animal models and humans, the biological process of anastomotic healing and the exact causes of AL are largely unknown. A recent hypothesis is that the pathophysiology of this entity involves a triad of local ischaemia, bacterial infection, and inflammation [4,5,6]. Furthermore, predisposing factors such as arteriosclerosis, diabetes, and lung disease have been associated as risk factors for the development of AL in patients undergoing oesophagectomy [7,8,9,10].

Endoscopic placement of a specially designed polyurethane foam at the level of the anastomosis with subsequent endoluminal negative pressure (ENP) therapy has a high success rate in treating AL [11,12,13]. The negative pressure continuously removes wound secretions, improving interstitial oedema and microcirculation, thus inducing tissue granulation which results in accelerated healing of the infected area. Moreover, a recent case series demonstrated that prophylactic ENP (pENP) in patients with proven local ischemia at the anastomosis was effective in preventing AL in six of eight patients. [14] However, in this study, the ENP device was placed during the early postoperative course after anastomotic ischemia was detected, whilst the present study evaluates a prophylactic application of ENP in patients identified to be high risk for developing AL. Recently, we have published a retrospective series of patients undergoing minimally invasive oesophagectomy with pENP therapy. Anastomotic healing was uneventful in 19/20 anastomoses resulting in a low AL rate of 5%. The single case of AL in these series successfully healed without further complications in response to a second course of ENP therapy. No adverse events attributable to pENP therapy were observed in this series [15].

The aim of the present study is to assess the effect of pENP placement at the anastomotic site on postoperative outcome following minimally invasive transthoracic oesophagectomy, with a focus on postoperative length of hospital stay and morbidity. The study is designed to address the following hypothesis: pENP therapy may reduce postoperative length of hospital stay and morbidity in high-risk patients undergoing total minimally invasive (laparoscopic and thoracoscopic) transthoracic Ivor Lewis esophagectomy (ttMILE).

## 2. Methods and analysis

The objective of this initiative is to assess the effect of pENP therapy in high-risk patients undergoing ttMILE on postoperative length of hospital stay, morbidity and mortality. The study has been reported in line with the Consolidated Standards of Reporting Trials (CONSORT) criteria [16].

The following hypotheses will be tested:

H0: Patients undergoing pENP after ttMILE have similar postoperative morbidity and hospital stay compared with patients who do not undergo pENP.H1: Patients undergoing pENP after ttMILE have a lower postoperative morbidity and a shorter hospital stay compared with patients who do not undergo pENP.

### 2.1. Registration

This trial has been registered with *ClinicalTrials.gov*, a primary registry in the WHO, on 14.11.2019 under the registration number NCT04162860 and with the Swiss National Clinical Trials Portal [*www.kofam.ch*] under the registration number SNCTP000003524.

### 2.2. Study design

This study is a prospective multi-centre, two-arm, parallel-group randomised controlled trial. The study flow chart is shown in ***Figure 1***.

**Figure 1 F1:**
[figure not shown]
Study flow chart of the randomized preSPONGE trial.

### 2.3. Study setting

The trial will be led by the Department of Visceral und Transplant Surgery, University Hospital Zurich, Zurich, Switzerland. The University Hospital Zurich is a high-volume expert centre for oesophageal surgery with an annual caseload of around 40 esophagectomies. In addition, we intend to recruit 3–4 additional European centres of similar caseload.

### 2.4. Sample size determination

Since no data is available on which sample size calculation could be based, a randomized pilot feasibility and safety study including 40 consecutive patients is planned.

For the completion of the formal preSponge RCT, additional patients will be included after definitive sample size calculation which will take place following inclusion of the first 40 patients in the feasibility study. It is anticipated that a total of 100 patients (approximately 50 per group) will be needed.

### 2.5. Inclusion and exclusion criteria

We will include adult high-risk patients (≥18 years of age) who provided informed consent and are scheduled for ttMILE. Robotic-assisted procedures will also be included.

Patients with **at least one of the following risk factors** will be considered at high risk for developing AL:

ASA score >2Diabetes (insulin dependent or HbA1c ≥ 6.5%)Chronic pulmonary disease (FEV1/FVC ratio ≤ 70%)Heart failure (LVEF <55%)Pre-existing cardiac arrhythmia (pacemaker or paroxysmal supraventricular tachyarrhythmia)Chronic kidney disease stage 4–5 (GFR < 30ml/min/1.73 m^2^)Chronic liver disease with portal hypertension (porto-caval pressure gradient ≥5–≤10mmHg, including patients with TIPS)Previous radiotherapy or chemo-radiation ≥50Gy (salvage oesophagectomy)

Alternatively, patients must have **at least two of the following risk factors**:

Arteriosclerosis score 2 according to van Rossum et al. [17] (aorta and coeliac axis)Malnutrition (BMI ≤ 18.5kg/m^2^)Obesity (BMI ≥ 35kg/m^2^)Heart failure with preserved ejection fraction (LVEF >55%)Active or former smokingAge > 65 yearsECOG/WHO/Zubrodt PS score > 1chronic kidney disease stage 2–3 (GFR 30–89 ml/min/1.73 m^2^)chronic liver disease without portal hypertension (porto-caval pressure gradient ≤5mmHg)

**Patients with fulfilling any of the following criteria will be excluded from the study:** 

Inability to provide informed consent or adhere to the study protocol, e.g. due to language problems, psychological disorders, or dementia.Patients younger than 18 yearsPatients scheduled for other technical variants of oesophagectomy, such as open, hybrid, or transhiatal procedures (intraoperative conversions to open access surgery will not be excluded)Chronic liver disease with portal hypertension (porto-caval pressure gradient >10mmHg)

### 2.6. Randomization, allocation and blinding

Randomization will be conducted with the use of an online randomization software (*http://randomizer.at*) one day prior to the scheduled surgical operation. The allocation ratio will be 1:1 and recorded in the software. The principle investigator or junior investigator will be responsible to generate the random allocation, enrolment and assignment of participants to interventions. Due to the nature of the intervention, blinding of participants and treating persons will not be feasible.

### 2.7. Methods of minimising bias

#### 2.7.1. Minimising selection bias

Consecutively screened and eligible patients will be included in the present study. A sufficient number of individuals will be recruited according to the sample size calculation (phase 2) in order to prevent random error and to achieve sufficient statistical power.

#### 2.7.2. Minimising performance bias

All esophagectomies will be performed in high-volume centres performing >20 minimally invasive esophagectomies per year [18]. Furthermore, the procedures will be performed by surgeons with a minimum case experience exceeding 100 oesophagectomies and pENP will exclusively be performed by interventional gastroenterologists or surgeons trained in ENP.

#### 2.7.3. Minimizing attrition bias

The trial will be reported according to the CONSORT statement [*www.consort-statement.org*]. The trial has been registered with *ClinicalTrials.gov* on 14.11.2019 with the unique identifying number NCT04162860 (*https://clinicaltrials.gov/ct2/show/NCT04162860*) and the Swiss National Clinical Trials Portal (SNCTP000003524). The trial protocol, including detailed description of clinical endpoints and statistical analysis plan will be published according to the SPIRIT statement [*www.spirit-statement.org*] to avoid risk of selective reporting.

#### 2.7.4. Other bias

Financial relationships with providers of medical devices or any conflict of interest that could inappropriately influence the work within this project will be stated explicitly [19]. The study design was conceived without any influence from the industry.

### 2.8. Trial organization

The principal investigator and the co-investigators are responsible for the preparation of the study protocol and the case report form (CRF). The principal investigator and the co-investigators are responsible for screening, recruitment, data collection and completion of the CRFs.

### 2.9. Interventions

#### 2.9.1. Explanation for the choice of comparators

It is not the current standard of practice to perform pENP during ttMILE in high-risk patients.

#### 2.9.2. Control Intervention

Patients in the control group will undergo a standard ttMILE without pENP. After 4–6 days, patency of the anastomosis will be assessed via either endoscopy, contrast radiography, or CT-scan, and results will be documented with a standard protocol.

#### 2.9.3. Experimental Intervention

Patients in the intervention group will undergo a standard ttMILE with pENP. After completion of the oesophago-gastric anastomosis, an Eso-SPONGE^®^ size 1 (overtube inner diameter 13mm, outer diameter 17mm) will be inserted via an intraoperative gastroscopy. pENP will be applied after completion of the oesophago-gastrostomy, but no later than 12 hours following the surgical intervention. The Eso-SPONGE^®^ device consists of an open-pored polyurethane foam fitted to a gastric tube. Postoperatively, secretions are continuously evacuated using a suction pump generating a negative pressure between 75–100 mmHg. The sponge is positioned under gastroscopic guidance at the level of the esophago-gastrostomy. ENP will remain in situ for 4–6 days and will be monitored based on clinical parameters (suction rate, vacuum leak rate, routine laboratory values, repeated routine chest x-rays). Discontinuation of ENP requires endoscopic removal of the Eso-SPONGE. During ENP removal, the anastomosis will be surveyed and documented with a standard protocol.

### 2.10. Outcomes

#### 2.10.1. Primary outcome pilot study

##### Feasibility

Feasibility will be assessed by assessing the number of eligible patients within the target population, recruitment rates, study refusal rates, study retention and follow-up rates as the participants move through the pilot study. Additionally, adherence rates to study procedures, intervention attendance, and engagement will be taken into consideration.

##### Safety

Any event of sponge-displacement, dislocation or intolerability will be recorded up to the 90-day postoperative follow-up period. Morbidity will be assessed using the Clavien-Dindo (CD) Classification [20] of postoperative complications, as well as the Comprehensive Complication Index (CCI) [21]. During the 90-day follow up period, the anastomotic stricture rate as a possible, anticipated adverse event of the ENP therapy will be recorded. Finally, the 90-day hospital readmission rate and mortality will be assessed.

#### 2.10.2. Primary outcome of the formal preSponge RCT

The primary outcome of the formal preSponge RCT will be postoperative length of hospitalisation. Patient discharge will be determined according to the subsequent, published, fit-for-discharge criteria [22].

The patients’ oral/enteral nutritional requirements are met by oral intake of at least liquids with optional supplementary nutrition via jejunal feeding tube.The patient should have passed flatus.The patient does not require oxygen during mobilisation (short walk or climbing stairs) or at rest.Central venous catheters should be removed before discharge (unless present preoperatively).Adequate analgesia at rest and during mobilization (pain score <4 on a scale from 0 to 10) is achieved using both oral opioid and non-opioid analgesics.All vital signs should be normal unless abnormal preoperatively.Inflammatory parameters (white cell count, C-reactive protein) should be trending down and close to normal.There should be adequate support after discharge (assistance by family, ambulatory nursing, or rehabilitation facility).The patient does not experience clinical deterioration precluding discharge having already achieved “fit-for-discharge” status.

#### 2.10.3. Secondary Outcomes

Secondary outcome measures include morbidity and mortality assessed by the CD Classification [20] and the CCI during the 90-day postoperative follow-up period. [21] Additionally, AL rate and grade, conduit necrosis, infections, wound healing problems, length of intensive care unit stay, hospital readmissions, stricture will be assessed during the aforementioned follow up period. No follow-up later than 90 days is planned.

### 2.11. Data management

Data will be entered in a CRF by the principal investigator or a designated surgical resident. For data and query management, monitoring, reporting and coding an online web-tool (*https://www.esoHub.org*/) that meets FDA standards will be used for this study. It is the responsibility of the investigator to assure that all data in the course of the study will be entered completely and correctly in the respective database. Corrections to the CRF may only be made by the investigator or by other authorized persons. In case of corrections, the original data entries will be archived in the system and can be made visible. For all data entries and corrections, the date, time of day and name of the individual performing the entries will be recorded automatically. All study data will be archived for a minimum of 10 years after study completion or premature termination of the clinical trial. All data will be stored on the server of the “Klinik für Viszeral- und Transplantationschirurgie, Universitätsklinik Zürich”.

### 2.12. Monitoring

An external committee will monitor the study. All original data including all patient files, progress notes and copies of laboratory and medical test results will be available for monitoring. The study monitors will review 20–30% of the eCRFs and written informed consents. The documentation of each site visit will be submitted to the ethics committee. The accuracy of the data will be verified by reviewing the above referenced documents. The investigator’s site will collaborate with the Clinical Trials Centre (CTC) of the University Hospital Zurich to ensure monitoring.

### 2.13. Safety and reporting of serious adverse events

Device deficiencies and all adverse events (AE) including all serious adverse events (SAE) are collected, fully investigated and documented in the source document and appropriate CRF during the entire study period, i.e. from patient’s informed consent until the last protocol-specific procedure, including a safety follow-up period. AE/SAEs will be reported to the principal investigator within 24 h of being noted. If the principal investigator considers a SAE as unexpected and related to the study intervention, they will submit a report to the ethics committee within three days. Documentation includes dates of event, treatment, resolution, assessment of seriousness and causal relationship to device and/or study procedure. In case of relevant differences between the morbidity and the SAEs between the groups, a report will be submitted to the local ethics committee. The trial may be terminated based on the decision of the principal investigator according to the assessment of the ethics committee.

### 2.14. Statistical analysis

Basic demographic, pre-, intra-, and postoperative, as well as follow-up data will be compared separately for each randomised group. Firstly, patients will be analysed according to intention-to-treat and secondly, per protocol. The potential for bias due to lack of adherence to the study protocol is of importance. A study-independent statistician will perform the intended primary statistical analysis after completion of the study.

The primary endpoint (length of hospital stay until “fit for discharge” criteria are reached) typically shows a skewed distribution and will be compared between the two groups with a Mann-Whitney U test. As for the secondary outcomes, the two groups will be compared according to the CD classification using the Pearson chi-square test [20,23]. The CCI will be compared between the two randomized groups using the Student t test [21]. AL- and mortality rate will be compared using Fisher’s exact test. A two-sided P value < 0.05 will be considered significant.

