The present study is the first randomised controlled trial that assesses the possible benefits of pENP therapy after ttMILE. Whilst the benefit of pENP has to be evaluated in a first step, another important question is the identification of the patient cohort that could benefit from this intervention. We believe that pENP could be especially beneficial in patients with multiple comorbidities who are at high risk for AL as defined by our inclusion criteria. The primary endpoint of the study (length of hospital stay until “fit for discharge”) was chosen to reflect a potentially faster short-term recovery. Although AL rate is an important secondary endpoint that may be reduced with pENP, our experience shows that more importantly, the course of AL occurring during pENP is remarkably more benign without septic complications. Therefore, pENP may seal potential full-thickness defects at an early stage thereby preventing free AL. If the results of the study are positive, the findings could potentially improve the postoperative management of patients undergoing oesophagectomy.

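### The unadjusted Mann-Whitney test chosen for the primary endpoint is valid, but it cannot use baseline risk information that the trial collects for eligibility; a pre-specified adjusted rank test would be more efficient at little or no cost

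*Protocol article*

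**What the plan says.** Section 2.14 fixes the primary analysis: the endpoint is expected to be skewed and "will be compared between the two groups with a Mann-Whitney U test". The significance rule is "A two-sided P value < 0.05 will be considered significant". No covariate, stratum or adjusted version is named. Section 2.6 gives 1:1 allocation and names no stratification factor. The only stated use of baseline data is this: "Basic demographic, pre-, intra-, and postoperative, as well as follow-up data will be compared separately for each randomised group".

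Section 2.5 admits patients who "will be considered at high risk for developing AL" because they have at least one of eight major factors, or alternatively at least two of nine lesser ones. Section 1 names arteriosclerosis, diabetes and lung disease as associated with leak. Section 3 expects the benefit to be greatest in "patients with multiple comorbidities who are at high risk for AL as defined by our inclusion criteria", and argues that fewer complications lead to a shorter stay.

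On sample size, section 2.4 says "Since no data is available on which sample size calculation could be based". It defers the definitive calculation until 40 patients are included and adds "It is anticipated that a total of 100 patients (approximately 50 per group) will be needed". No effect size, standard deviation or power is stated.

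**The concern.** Eligibility turns on characteristics that the protocol links to leak and, through complications, to length of stay. The entry rule still allows a wide spread. A former smoker over 65 qualifies on two lesser factors, and so does a patient with several major comorbidities. If these characteristics explain part of the variation in stay, a test that ignores them needs more patients to detect the same effect.

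What is at stake is efficiency: some power at a fixed sample size, or some patients at a fixed power. The protocol itself names the primary test. An adjusted version introduced later would therefore replace a published primary analysis, in a trial where participants and treating staff are not blinded. It is better decided now.

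**Working it through.** **Inputs from the protocol article.** Two-sided alpha 0.05 and the Mann-Whitney test (section 2.14); about 50 per arm, provisional (section 2.4); 1:1 allocation (section 2.6).

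**Inputs that are assumed.** The standardised effect d on the log-stay scale, the spread and median of stay, and R2, the share of within-arm variance of log stay explained by baseline factors. The protocol gives none of these, so R2 is varied from 0 to 30%.

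**The plan's own figure.** The total of 100 has no stated inputs and can be neither reproduced nor refuted. It can only be solved backwards. With Mann-Whitney efficiency 3/π = 0.955, the effect detectable at 80% power is

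d = (1.960 + 0.842) × √(2 / (50 × 0.955)) = 0.573.

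**Normal approximation.** Adjustment shrinks the residual SD by √(1 − R2), so

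power = Φ( d / √(1 − R2) × √(50 × 0.955 / 2) − 1.960 ).

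| R2 | d = 0.5 | d = 0.573 |
|---|---|---|
| 0 | 68.5% | 80.0% |
| 5% | 70.8% | 82.0% |
| 10% | 73.1% | 84.0% |
| 20% | 78.0% | 87.9% |
| 30% | 83.1% | 91.8% |

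This is slightly optimistic, because covariates explain somewhat less of the ranks of whole-day stays than of log stay itself.

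**Simulation, 50 per arm, log-normal stay rounded up to days.** Each cell shows Mann-Whitney power, then rank ANCOVA power.

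- Setting A: median 14 days, SD of log stay 0.6, log effect −0.30. This is a 26% shorter stay, since 1 − exp(−0.30) = 0.26, and d = 0.30 / 0.6 = 0.5. There are two baseline covariates and 6,000 runs per cell.
- Setting B: d = 0.573, one baseline score, 8,000 runs per cell.

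| R2 | Setting A | Gain | Setting B | Gain |
|---|---|---|---|---|
| 0 | 67 v 67% | 0 | 79.6 v 79.4% | about 0 |
| 5% | 68 v 69% | 1 | 78.9 v 80.0% | 1.1 |
| 10% | 68 v 72% | 4 | 79.3 v 82.3% | 3.0 |
| 20% | 68 v 77% | 9 | 79.4 v 86.7% | 7.3 |
| 30% | 67 v 81% | 14 | 79.5 v 90.5% | 11.0 |

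A repeat of setting A with a different random seed gave gains of 1.7, 3.7, 7.9 and 13.6 points at R2 5%, 10%, 20% and 30%. Allowing for simulation error, the gain is about 0-2 points at R2 5%, 2-4 at 10% and 7-9 at 20%. With no treatment effect, both tests rejected in about 4.4-5.2% of runs throughout.

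**In patients.** The formula 1 / (1 − R2) equates adjustment to 11% more patients at R2 10% and 25% more at R2 20%. Converting the setting B powers through their normal quantiles gives less: ((1.960 + 0.927) / (1.960 + 0.816))² = 1.08 at R2 10%, and ((1.960 + 1.110) / (1.960 + 0.820))² = 1.22 at R2 20%. So adjustment is worth roughly 8% and 22% of the sample in this setting.

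**The case against.** The strongest reply is that nothing in section 2.14 is wrong. The Mann-Whitney test is a conventional choice for a skewed outcome, and it keeps its error rate. This stands, and it sets the weight of the point.

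A reader might infer several stronger claims. The document does not support them.

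- **The trial is underpowered.** No power is stated and the sample size is still to be calculated. A number computed for the Mann-Whitney test can reach its target; the cost is then extra patients.
- **Chance imbalance in risk makes the result biased.** Under randomisation, such imbalance is already part of the test's null distribution and its 5% error rate. Adjustment improves precision; it does not repair a bias.
- **Every listed factor is on record for every patient.** One major factor or two lesser ones suffice for entry, so complete recording of all 17 can only be inferred. A count of factors might need extra data.
- **Baseline significance tests are planned.** The text speaks of comparing baseline data, which does not clearly mean testing them.
- **The factors are known to drive length of stay.** The protocol links them to leak and reaches stay only through complications. Section 1 puts leak at 5-30% of patients, and restricting entry to high-risk patients may narrow the prognostic spread. R2 could therefore be small.

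It can also be said that an adjusted analysis belongs in a statistical analysis plan that is not shown. That holds for a supplementary analysis. It does not hold for the primary test, which the article itself fixes.

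**Conclusion.** The point holds as an efficiency improvement that is free or cheap, not as an error. The stated primary test is unadjusted, and it cannot use baseline information that is assessed before randomisation and that the protocol considers prognostic for leak. At R2 10-20% the adjusted test is worth having; at 5% or below it makes practically no difference. The direction is secure: in the simulations adjustment cost no meaningful power even at R2 0, and type I error was unaffected. The size is not secure, because it rests on assumed values of R2, effect, median and spread. Whether the loss would be met as lower power or as more patients depends on the sample-size calculation still to come.

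**What to change.** In section 2.14, before any between-arm comparison is made, name one primary test: a rank analysis of covariance of time to fitness for discharge. Rank stay across all patients, regress the ranks on the covariates without treatment, and compare the residuals between arms at two-sided 0.05.

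Pre-name two or three covariates known for every patient before randomisation, for example age as a continuous variable, ASA class, and whether the one-factor list is met. ASA above 2 by itself meets that list, so the last two overlap; this does not harm the test, but age plus one of them may be enough. Use the count of all listed factors only if every item is recorded in all patients. Keep the unadjusted Mann-Whitney test as a sensitivity analysis.

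The first 40 patients, with arms pooled, can indicate how much variation in stay the covariates explain before the definitive sample size is set.

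The cost is about two sentences, with no added procedures or patients. The covariates must be fixed in advance, little or nothing is gained if they are weakly prognostic, and rank ANCOVA does not itself give an effect in days, so stay by arm should still be summarised in days.

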## 3. Discussion

This prospective multi-centre, parallel-group RCT aims to assess the effect of pENP on AL after ttMILE in high-risk patients. We hypothesise that patients at increased risk for AL undergoing pENP suffer from fewer postoperative complications and therefore have a reduced length of hospital stay and reach “fit for discharge” criteria faster. Until now, endoscopic placement of the polyurethane foam at the level of the anastomosis with ENP has been exclusively used for the treatment of AL, whilst published data regarding its prophylactic application remains scarce [11,12,13,24,25]. In an experimental pilot study by Scott et al. on pigs undergoing Ivor Lewis esophagectomy, experimental anastomotic defects were treated with pENP or received no specific treatment. Half of the pigs in the control group died within 24 hours and were excluded from analysis, whereas the surviving controls showed frank AL and pleural contamination with gastric contents. In contrast, no leaks were detected in the ENP cohort after 3–7 days follow-up (p = 0.03). This study demonstrated that pENP may have the potential to close leaks that otherwise would persist without surgical or endoscopic intervention [26]. Further evidence supporting this hypothesis stems from our own Institution’s retrospective case-series of 20 consecutive patients undergoing minimally invasive oesophagectomy with pENP, anastomotic healing was uneventful in 19/20 anastomoses resulting in an AL rate of 5%. One contained AL healed without further complications following a second course of ENP. There were no adverse events attributable to pENP therapy [15].

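### Fisher's exact test for anastomotic leak is valid but conservative at about 50 per arm; Boschloo's exact test keeps the 5% limit and gains roughly 1 to 8 points of power

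*Protocol article*

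**What the plan says.** The statistical section (2.14) names the test for leak and mortality: "AL- and mortality rate will be compared using Fisher’s exact test". The threshold follows: "A two-sided P value < 0.05 will be considered significant".

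The size of the trial is provisional. Section 2.4 states "It is anticipated that a total of 100 patients (approximately 50 per group) will be needed" and leaves the definitive number to a calculation after the first 40 patients. Section 2.6 adds "The allocation ratio will be 1:1 and recorded in the software". No power is stated for leak or mortality.

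Leak is a secondary outcome (2.10.3), but the Discussion gives it weight. It says that the trial "aims to assess the effect of pENP on AL after ttMILE in high-risk patients" and, of its rank, "Although AL rate is an important secondary endpoint that may be reduced with pENP". The primary outcome is length of stay, compared by a Mann-Whitney test.

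**The concern.** Fisher's test conditions on the total number of events. With few events the attainable P values are coarse, so the real type I error can lie well under the nominal 5%, and the unused part is lost power. The leak comparison is already weak at about 50 per arm.

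Some remedies, such as the mid-P version, give up the guaranteed error limit, and then the choice is a matter of taste. Boschloo's test gives up nothing of that kind, so the question is how much power it recovers.

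The practical stake is a result near the boundary. At 50 per arm, 9 leaks on control and 2 with the device give a Fisher P value of 0.051. That would be reported as not significant, although a test with the same 5% guarantee would reject.

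**Working it through.** **Inputs**
- Test, level and sidedness: section 2.14.
- About 50 per arm, 1:1: sections 2.4 and 2.6.
- Control leak rate: the Background states "AL occurs in 5–30% of patients after esophagectomy". Rates of 10, 15, 20, 25 and 30% are used as assumptions inside that range.
- Leak rate with the device: 1 of 20 = 5%, from the retrospective series in the Background.

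The plan states no power for leak, so there is no figure of its own to reproduce.

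**Method.** For arms of size n1 (control) and n2 (device), list every pair of leak counts (x, y); at 50/50 that is 51 × 51 tables. Compute the two-sided Fisher P value of each.
- Fisher's rejection region: P < 0.05.
- Boschloo's region: P ≤ c, where c is the largest cut-off for which the type I error, maximised over the common rate, stays at or below 0.05.
- Size at common rate p: the sum over the region of Bin(x; n1, p) × Bin(y; n2, p).
- Power at rates p1, p2: the sum over the region of Bin(x; n1, p1) × Bin(y; n2, p2).

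Fisher's own region already has size at most 0.05, so c cannot be below Fisher's cut-off. Boschloo's region therefore contains Fisher's, and its power is at least as high at every pair of rates.

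**Type I error at 50/50.** The Boschloo cut-off is c = 0.0693.
- Fisher: maximum 3.52%; 0.72% at a common rate of 5%, 1.8% at 10%, 2.8% at 20%, 3.1% at 30%.
- Boschloo: maximum 4.87%.

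**Type I error at unequal splits of 100.** Fisher's maximum is 4.6% at 49/51 and 4.4% at 48/52.

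**Power for leak at 50/50, device rate 5%**

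| Control rate | Fisher | Boschloo | Gain (points) |
|---|---|---|---|
| 10% | 6.3% | 10.9% | 4.6 |
| 15% | 24.4% | 32.1% | 7.8 |
| 20% | 50.8% | 58.3% | 7.5 |
| 25% | 74.8% | 79.9% | 5.1 |
| 30% | 89.9% | 92.5% | 2.6 |

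Gains are taken before rounding.

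**Gain in points at other splits of 100 (control/device), device rate 5%**

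| Control rate | 49/51 | 48/52 | 52/48 |
|---|---|---|---|
| 10% | 4.5 | 2.9 | 5.2 |
| 15% | 4.1 | 3.1 | 8.1 |
| 20% | 3.1 | 2.0 | 6.7 |
| 25% | 2.1 | 1.4 | 3.8 |
| 30% | 1.1 | 0.9 | 1.6 |

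Across both tables the gain runs from about 1 to about 8 points.

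**Other sample sizes.** For 20% v 5% and 25% v 5% the gains are 3.7 and 1.5 points at 80 per arm, and 2.0 and 0.4 at 100 per arm. The fall is not strictly monotone: at 55 per arm, 15% v 5% gains 10.0 points.

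**Boundary tables at 50/50** (control v device), not significant by Fisher but inside Boschloo's region because P ≤ 0.0693: 9 v 2 (P = 0.051), 12 v 4 (0.054), 5 v 0 (0.056), 7 v 1 (0.059).

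**The case against.** The strongest reply is that nothing here is wrong. Fisher's test holds the stated level, it is the conventional choice for sparse 2×2 tables, and leak is a secondary endpoint. All of that stands and limits the point to a cheap improvement.

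A second reply is that the loss depends on the exact split, and this also stands. Section 2.4 says only approximately 50 per group, and exactly equal arms are unusually unfavourable to Fisher's test. With 48 or 49 control patients the leak gain falls to about 1–4.5 points.

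A reader might infer that Fisher's test runs far below 5% in general, and costs 5 to 11 points for both leak and mortality. The document does not support that:
- The low maximum size of 3.5% belongs to the exact 50/50 split.
- With Boschloo's test at 50 per arm, a gain of 11 points appears for 10% v 2% (19.0% to 30.4%), and 2% lies outside the 5–30% range in the Background. For leak against 5%, a gain of that order at 50/50 needs a different exact unconditional test based on the pooled z statistic (10.6 points for 20% v 5%).
- At the top of the quoted range, 30% v 5%, the gain is under 3 points.
- No mortality rate is given. At an assumed 3% v 1%, power at 50/50 is 0.2% with Fisher and 1.0% with Boschloo, which changes nothing in practice.

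What survives is that the replacement guarantees the same error limit and cannot lose power, so preferring it is not a trade of level against power.

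**Conclusion.** The point holds as a modest gain in efficiency on a secondary endpoint. At a total of about 100 patients, Boschloo's test adds roughly 1 to 8 points of power for leak under the same two-sided 5% limit. This rests on assumed control rates of 10–30%, on a device rate of 5% taken from one leak in 20 patients, and on a sample size that the plan calls only anticipated. The change does not rescue the comparison where the true difference is small: at 10% v 5%, power stays near 11% at 50/50. Section 2.14 is neither wrong nor contradicted elsewhere, and the primary analysis of length of stay is untouched.

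**What to change.** In section 2.14, name Boschloo's exact unconditional test in place of Fisher's for the leak comparison, at the same two-sided 5% level. State that the test statistic is the two-sided Fisher P value and that the type I error is maximised over the common rate, since the figures above rest on that definition. Use the same test for mortality for consistency only, without claiming a gain.

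The change must be fixed before outcome data are seen and reported by the route for modifications in section 2.15. It costs one line of text and no patients, and standard software provides the test. The downside is that readers know it less well than Fisher's test.
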